##### Secondary outcome measures in included patients

All-cause mortality in included patients. Number of deaths will be collected from national and regional registries [Time Frame: 3 years].Overdose mortality in included patients [Time Frame: 3 years].Retention in naloxone program - number of patients [Time Frame: 3 years].Incidence of witnessing opioid overdoses [Time Frame: 3 years].Incidence in naloxone use and bystander pulmonary resuscitation [Time Frame: 3 years].

#### Power and sample size

Power has been calculated only for the primary outcome measure. The total population at risk of fatal overdose in the general population is unknown, as people may be at risk of overdose death either because of a severe opioid dependence, a less severe state of dependence or a more unregular use of opioids. As the number of potentially affected individuals is unknown, the power calculations were based on numbers calculated from the number of individuals reached by the intervention at NEP and OST facilities. Thus, power calculations based on the cohort planned to receive distributed naloxone will be considered to be a minimum level with the possibility of a higher effect if the naloxone intervention disseminates also beyond the NEP and OST populations.

The number of patients in OST and NEP is estimated to comprise approximately 2000 individuals, 1000 individuals respectively. Power was calculated based on potential mortality in these two groups (calculated conservatively for 4 years prior to the intervention); a total of 4 × 2000 = 8000 person years; referred to as a ‘comparison period’), and with the conservative assumption that the intervention is calculated to reach the full study group for 1.5 years (intervention group, 2019–2020) (1.5 × 2000 = 3000 person years). The statistical power calculations are made with the Microsoft Excel sheet EPISHEET available for download at www.krothman.org/episheet.xls (downloaded on 14 January 2016).

Assuming that mortality before intervention is 50 deaths per 1000 person years in the overall cohort (that is, a 5% annual risk), a relative risk reduction of 25% (relative risk RR = 0.75) is required in order for the statistical strength to exceed 80% (81%), 5% significance limit, two-sided test, with 8000 person years before intervention (comparison period) and 3000 person years after intervention (intervention group). If however, assuming that mortality before intervention is 30 per 1000 person years in the overall cohort (that is, a 3% annual risk), a higher relative risk reduction, 32% (RR = 0.68), is required for the statistical strength to exceed 80% (81%), 5% significance limit, two-sided test, with 8000 person years before intervention (comparison period) and 3000 person years after intervention (intervention group). If the risk reduction still is 25%, even in this scenario, the statistical strength drops to 57%.

Based on previous studies from other types of settings, one can assume that, during follow-up, 10–20% of those who received naloxone have used these doses [87–89]. It is not possible to establish how many of those given naloxone, in an overdose situation, would have died if the dose had not been administered. It is also not possible to draw conclusions from the literature on how often a person with access to naloxone can be expected to be present when an overdose occurs. With a reduction in number of deaths (per 1000 person years) from 30 to 20 individuals, in regards to the power calculation above, and assuming that only 10% of those receiving naloxone use the dose, 100 (10 × 10) present overdose witnesses are required with access to naloxone for dose to be given in ten cases. With a careful estimate of how often an overdose will be witnessed by someone carrying, or having access to, naloxone, it is our belief that 2000 study participants, with a plan for inclusion of around 1000 patients from OST and 1000 patients from NEP, will be sufficient in order to detect significant reductions in mortality. In addition, the present calculations cautiously assume that the spread of naloxone will take place primarily within the NEP and OST populations. Although the individuals receiving naloxone in the program are either NEP or OST clients, it also should be borne in mind that theoretically, broader groups of individuals at risk of opioid overdoses may benefit from the intervention in case of naloxone spreading outside the core populations seen in the project.

In addition to the effects studied above, the correlation will be calculated between the number of distributed doses in the study cohort and the effects on the outcome variables above.

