### Opioid overdose mortality in Sweden

Reported incidence of drug related death is approximately four times higher in Sweden (92 deaths/million) [3] compared to the average of Europe (22.6 deaths/million) [1]. Acute onset lethal intoxications have gradually increased since 1991, accompanied by an increase of deaths involving other opioids such as buprenorphine, fentanyl, methadone and tramadol [1, 76]. Toxicology records show that opioids are present in 95% of the drug related deaths. These records also show a high, and increasing, proportion of cases exhibiting the presence of more than one substance, indicating that poly-drug use, to a large extent, contributed to their death. The slight decrease in numbers of drug related deaths between 2015 and 2016 unfortunately proved to be a short break in the otherwise increasing numbers [1–3], showing that these numbers do fluctuate over time, adding to the challenging task of drawing conclusions from the result of interventions.

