## Methods/design

### Setting

The present setting is the county of Skåne, the southernmost county of Sweden with around 1.3 million inhabitants. The major city of the region is the city of Malmö, with around 315,000 inhabitants, and three other major cities (Helsingborg, Lund, and Kristianstad) with populations of 145,000 to 85,000 inhabitants. By Swedish measures, the region of Skåne has unique access to both needle exchange programs (NEP) and opioid substitution treatment (OST) clinics through a network of units which enable reaching a large proportion of illicit drug users at risk of an opioid overdose. The Skåne region has seen a considerable expansion of OST in recent years, and in November 2017, a total of 1514 patients were enrolled in OST in the region. The region has four NEPs, in the four largest cities of the region, and which are open on weekdays and administered by the departments of infectious diseases within the regular hospital system. Altogether, the NEPs of the region have around 1000 to 1100 patients enrolled annually. The number of people at risk of an opioid overdose in the region is likely difficult to establish, as overdoses may occur both to patients known in addiction treatment or harm reduction, based on their opioid dependence, but also to unregular opioid users including patients seen in treatment for other addictive disorders and who may occasionally misuse opioids.

Overdoses in the present region have been examined in several papers during the past decade. For example, it was documented in qualitative interviews that despite an overall willingness from heroin users to help peers who overdose, several potential barriers against adequate interventions by bystanders were identified, such as uncertainty about the victim’s own intentions, the influence of one’s own intoxication, and fear of police when calling the ambulance [81]. Also, a smaller survey carried out in OST patients in the same region demonstrated high prevalence of overdoses, but also a very high interest in participating in a potential naloxone program [78].

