#### Primary outcome measures

Mortality due to opioid intoxication in the general population in Skåne County in 2019–2023, compared with historical mortality due to opioid intoxication during 2013–2017. Number of deaths will be collected from national registries.

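### The 81%/81%/57% power is for mortality in about 2000 OST/NEP clients, not for county opioid deaths, and it is not a lower bound for the primary comparison

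*Protocol article*

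**What the plan says.** The Primary outcome measures section defines the outcome as "Mortality due to opioid intoxication in the general population in Skåne County in 2019–2023", compared with 2013–2017. Study aims agrees that the primary aim concerns the general population of the region.

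The Power and sample size section opens with "Power has been calculated only for the primary outcome measure". Because the number of people at risk is unknown, it turns to OST and NEP clients: "Power was calculated based on potential mortality in these two groups". The comparison period is "a total of 4 × 2000 = 8000 person years" and the intervention period is 1.5 × 2000 = 3000 person-years. One scenario begins "Assuming that mortality before intervention is 50 deaths per 1000 person years in the overall cohort"; the others use 30 per 1000. No cause of death is specified. The results are 81% (50 per 1000, RR 0.75), 81% (30 per 1000, RR 0.68) and 57% (30 per 1000, RR 0.75). The section adds that "power calculations based on the cohort planned to receive distributed naloxone will be considered to be a minimum level", since naloxone may spread further.

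Statistical methods contains a sentence tying the primary outcome to mortality in the overall cohort. The same section gives 2013–2017 v 2019–2023 for the population analyses and says that secondary outcomes were not powered. Trial status places the first population analysis at 18 months (July 2019 to December 2020).

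**The concern.** The calculation and the outcome concern different deaths. The calculation counts deaths of any cause among 2000 clients. The outcome counts opioid-intoxication deaths among 1.3 million inhabitants, including people never seen at OST or NEP.

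The minimum-level argument considers one direction only. Spread beyond the cohort can add prevented deaths, so the number prevented within the cohort may be a minimum. Power for a county rate ratio also depends on the deaths that are not prevented. The plan accepts that people outside the cohort are at risk, in unknown number, and assumes that spread is mainly within NEP and OST. Dilution therefore follows from its own assumptions.

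Nor does the unknown number at risk force the use of the cohort. A before/after Poisson comparison of county deaths needs expected death counts, and the plan takes these from national registers.

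At stake is how a null result is read, especially at 18 months, which matches the 1.5 years in the power text. A reader would set it against an 81% that was never the power of that comparison.

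**Working it through.** **1. Reproducing the stated figures.** Two-proportion formula, two-sided 5%, n0 = 8000, n1 = 3000. For 50 per 1000 and RR 0.75: p0 = 0.05, p1 = 0.0375, pooled p = (400 + 112.5)/11000 = 0.0466. The null SE is 0.00451 and the alternative SE 0.00424. Power = Φ((0.0125 − 1.96 × 0.00451)/0.00424) = 80.6%. The other two scenarios give 80.4% and 57.0%. All three agree with the text as cohort-mortality figures.

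**2. One formula for cohort and county.** To avoid mixing methods, use Wald: power = Φ(|ln RR| / √(1/D0 + 1/D1) − 1.96), where D0 and D1 are expected deaths before and after. The cohort scenarios have D0/D1 of 400/112.5, 240/61.2 and 240/67.5, and give 77%, 77% and 55%. These are the like-for-like reference.

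**3. The floor claim at equal windows, without a county total.** Take 100 cohort deaths a year, RR 0.75, 4 v 1.5 years, and add untouched outside deaths to both periods:
- none: RR 0.75, power 77%
- 25 a year: RR (75 + 25)/125 = 0.80, power 67%
- 50 a year: RR (75 + 50)/150 = 0.833, power 59%

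The same deaths are prevented each time, and power still falls.

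**4. An approximate county baseline.** Opioid overdose mortality in Sweden reports: "Reported incidence of drug related death is approximately four times higher in Sweden (92 deaths/million"; it also says opioids are present in 95% of drug-related deaths. Setting describes "the county of Skåne, the southernmost county of Sweden with around 1.3 million inhabitants". So 92 × 1.3 × 0.95 ≈ 114 a year. Applying the national rate to Skåne, and reading opioid presence as opioid intoxication, are assumptions. If the rate refers to only about 64% of inhabitants (also an assumption), the count is 114 × 0.64 ≈ 73.

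**5. County power at 114 a year,** with all cohort deaths opioid-related and no outside effect. County RR = 1 − (cohort deaths prevented per year)/114.

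| Scenario | Prevented per year | County RR | Cohort power (Wald) | 4 v 1.5 y | 5 v 1.5 y | 5 v 5 y |
|---|---|---|---|---|---|---|
| 50/1000, RR 0.75 | 100 × 0.25 = 25 | 0.781 | 77% | 71% | 73% | 97.5% |
| 30/1000, RR 0.68 | 60 × 0.32 = 19.2 | 0.832 | 77% | 48% | 50% | 84% |
| 30/1000, RR 0.75 | 60 × 0.25 = 15 | 0.868 | 55% | 32% | 33% | 63% |

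Worked case, row 2, 4 v 1.5 years: D0 = 4 × 114 = 456 and D1 = 1.5 × 114 × 0.832 = 142. Then |ln RR| = 0.184, SE = 0.096, and Φ(1.92 − 1.96) = 48%.

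At 73 a year the two 30-per-1000 scenarios give 70% and 49% for 5 v 1.5 years, and 97% and 83% for 5 v 5. The 50-per-1000 scenario cannot be run there with all deaths opioid-related, since 100 exceeds 73.

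**6. If only part of cohort deaths are opioid intoxications** (114 a year, 5 v 5 years, same cohort RR applied to the opioid deaths):
- 70%: prevented 17.5, 13.4 and 10.5 a year; power 77%, 54% and 36%
- 50%: prevented 12.5, 9.6 and 7.5 a year; power 48%, 31% and 20%

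**7. Detectable county RR at 80% power** (5-year baseline): about 0.76 at 18 months and 0.84 for 5 v 5 years at 114 a year; about 0.70 and 0.80 at 73 a year.

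**The case against.** The strongest reply is that the outcome compares five years with five, while the power text deliberately used shorter, conservative windows. On the 5 v 5-year comparison the table gives 97.5%, 84% and 63%, all above the stated 81%, 81% and 57%. This stands under the assumptions in step 5. A reader might infer that the final primary analysis is underpowered; those figures do not show it. But the longer window produces the gain, and it is lost when a good part of cohort deaths are not opioid intoxications (step 6). The plan gives no opioid-specific cohort rate to settle this.

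Second, setting the county 73% against the stated 81% would overstate the loss, because the stated figure comes from a different formula. This also stands; the fair reference is 77%.

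Third, a reader might infer that 50 per 1000 is implausible, since it means 100 cohort deaths a year against 114 opioid deaths in the county. The document does not support that: its cohort rate is not restricted by cause, so the counts are not comparable.

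Fourth, no effect outside the cohort is a limiting case, because the plan allows for spread. True, but it gives no size for spread, and a possible gain does not make the figure a floor.

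Last, under the overall-cohort sentence in Statistical methods, the calculation would match the outcome. That sentence conflicts with Study aims and Primary outcome measures, so it is part of the defect.

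**Conclusion.** The point holds in limited form. The stated power belongs to unrestricted mortality in the OST/NEP cohort, and the minimum-level claim does not follow: at the plan's own windows any untouched outside deaths lower the power.

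The loss is modest in the 50-per-1000 scenario (77% to 71%) and large in the 30-per-1000 scenarios (77% to 48%, 55% to 32%). It is much the same for the 18-month first analysis. For the 5 v 5-year comparison a shortfall is possible but not demonstrated; it depends on the opioid share of cohort deaths.

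The sizes rest on a national rate applied to Skåne, the 95% figure, no effect outside the cohort, the assumed opioid share of cohort deaths, and Poisson variation without secular trend or overdispersion. That the calculation does not match the defined outcome, and that the floor claim fails at equal windows once outside deaths are counted, needs no estimate of the county total.

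**What to change.** - Reconcile the overall-cohort sentence in Statistical methods with Study aims and Primary outcome measures, so that one primary outcome is defined.
- Restate power, or the detectable RR, on expected county opioid-intoxication deaths, using the 2013–2017 register count as baseline. Give it separately for the 18-month and the 5 v 5-year comparisons. The values in step 7 are a guide until the register count is used.
- Label 81%/81%/57% as cohort-mortality figures, and amend the statement that secondary outcomes were not powered so that the two agree.
- Delete the minimum-level claim. Spread can still be mentioned as a possible gain, alongside dilution as a possible loss.

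The cost is one restated paragraph, two conforming sentences in Statistical methods and a less favourable figure for the 18-month analysis. No sample size, data source or analysis window has to change.

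### The 81% power at RR 0.75 is not supported as power for the primary outcome: its 50 deaths per 1000 person-years is either too large a share of county opioid deaths or not an opioid-death rate

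*Protocol article*

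**What the plan says.** Under Primary outcome measures, the protocol article defines the endpoint as "Mortality due to opioid intoxication in the general population in Skåne County in 2019–2023", to be compared with 2013–2017. Under Power and sample size it states: "Power has been calculated only for the primary outcome measure".

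That calculation uses about 2000 OST and NEP clients, with 8000 person-years before and 3000 after the intervention and a two-sided 5% test. It gives two scenarios:

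- The first begins "Assuming that mortality before intervention is 50 deaths per 1000 person years in the overall cohort (that is, a 5% annual risk"), and arrives at 81% power for RR 0.75.
- The second assumes 30 per 1000. It needs RR 0.68 for 81% power, and has 57% power at RR 0.75.

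Neither rate has a source, and neither is described as all-cause or as opioid-specific.

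Elsewhere the article supplies figures against which the rates can be checked. The section on overdose mortality in Sweden puts the incidence of drug-related death as "approximately four times higher in Sweden (92 deaths/million"), and adds: "Toxicology records show that opioids are present in 95% of the drug related deaths". The Setting section describes Skåne as "the southernmost county of Sweden with around 1.3 million inhabitants".

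**The concern.** A power figure said to be for opioid-intoxication deaths needs a baseline rate of opioid-intoxication deaths. A rate of 50 per 1000 in 2000 people is a large number of deaths for a county of this size. The article also says, under Setting, Power and sample size, and Opportunities and challenges, that less dependent, irregular and prescription-opioid users outside OST and NEP are at risk too.

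For a 25% reduction, the 50-per-1000 scenario is the only one printed that meets the 80% target set under Statistical methods. If its baseline is too high for the endpoint, or belongs to another endpoint, the article has no supported statement of 80% power for a 25% reduction in the primary outcome.

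**Working it through.** **1. Reproduce the stated power.** Treat person-years as the two sample sizes, n0 = 8000 and n1 = 3000, and compare two proportions with pooled variance under the null:

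power = Φ[(p0 − p1 − 1.96·SE0) / SE1], where SE0 = √[p̄(1 − p̄)(1/n0 + 1/n1)] and SE1 = √[p0(1 − p0)/n0 + p1(1 − p1)/n1].

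For p0 = 0.050 and p1 = 0.0375: p̄ = (400 + 112.5)/11000 = 0.0466, SE0 = 0.00451, SE1 = 0.00424. Power = Φ[(0.0125 − 0.00884)/0.00424] = Φ(0.86) = 80.6%.

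| Baseline per 1000 | RR | Stated | Recomputed |
|---|---|---|---|
| 50 | 0.75 | 81% | 80.6% |
| 30 | 0.68 | 81% | 80.4% |
| 30 | 0.75 | 57% | 57.0% |

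The power arithmetic is sound. The question is the baseline rate.

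**2. Deaths the rates imply in the cohort.**

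- 50 per 1000: 0.050 × 2000 = 100 a year.
- 30 per 1000: 0.030 × 2000 = 60 a year.

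**3. Opioid-involved deaths in the county.** The article gives no Skåne rate, so the national rate is applied as an assumption: 1.3 million × 92 per million = 119.6 drug-related deaths a year; × 0.95 = 113.6 with opioids present.

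**4. Share of county deaths that must fall in the cohort.** The two higher county rates are assumptions, chosen to show the sensitivity.

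| Assumed county rate per million | County opioid-involved deaths a year | Share at 50 per 1000 | Share at 30 per 1000 |
|---|---|---|---|
| 92 | 113.6 | 100/113.6 = 88% | 60/113.6 = 53% |
| 110 | 1.3 × 110 × 0.95 = 135.9 | 74% | 44% |
| 130 | 1.3 × 130 × 0.95 = 160.6 | 62% | 37% |

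A county rate below the national one would raise these shares.

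**5. The all-cause reading.** If 50 per 1000 counts deaths from any cause, step 4 does not apply. The endpoint is then all-cause mortality, which the article lists as a secondary outcome in included patients. If opioid deaths are a fraction f of all deaths and only they respond, a 25% fall in all deaths needs a fall of 25%/f in opioid deaths, which exceeds 25% whenever f is below 1.

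**6. The county-wide comparison, as a check on how far the point reaches.** Take 113.6 deaths a year, a 25% county-wide fall and a simple Poisson comparison, with power = Φ[|ln 0.75|/√(1/a + 1/b) − 1.96], where a and b are the expected deaths before and after.

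- 5 v 1.5 years: a = 568, b = 113.6 × 0.75 × 1.5 = 128; power about 84%.
- 5 v 5 years: a = 568, b = 426; power about 99%.

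Both ignore time trend and overdispersion, and both assume that the 25% fall occurs across the whole county.

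**The case against.** The strongest reply is that nothing has been miscalculated and the weaker case is already disclosed. All three powers reproduce. The 57% at 30 per 1000 is printed beside the 81%, RR 0.75 is given as the reduction each scenario would need and not as the expected effect, and the later argument that 2000 participants suffice works from a fall from 30 to 20 per 1000. This stands, and it makes the correction smaller. It does not supply a basis for the 50-per-1000 scenario.

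The 88% also depends on a national rate carried over to one county. That stands as well, and the share falls to 62% at 130 per million.

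The rate may have been meant as all-cause. Statistical methods refers to mortality in the overall cohort and records alive or dead status, which favours that reading. The 88% would then fall away, but the statement that power was computed for the primary outcome would be wrong.

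The article calls its calculation a minimum. That refers to benefit spreading beyond the cohort; it does not make a high baseline conservative.

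Three stronger inferences are tempting but not supported:

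- **That the rate implies more deaths than the county has.** Adding the OST enrolment ("a total of 1514 patients were enrolled in OST in the region") to 1000–1100 NEP clients gives 2514–2614 people and 126–131 deaths a year at 50 per 1000. This needs almost no overlap between the services: it takes more than about 2272 distinct people (113.6/0.050) to pass 113.6. The OST count is also from November 2017, after an expansion, and need not describe the comparison period.
- **That true power for a 25% reduction is some specific lower range.** Any such range needs the share of county opioid deaths that occur among clients, which the article does not give. Its 70% figure for the Malmö NEP is reach among people who inject in that catchment area, not a share of deaths.
- **That the trial is underpowered.** The stated primary comparison is county-wide, and step 6 gives about 84% or 99% for a 25% county-wide fall. An effect confined to clients would be diluted, but that is a separate question.

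**Conclusion.** The point holds in limited form. The 81% power at RR 0.75 is unsupported as power for the primary outcome on either reading of its baseline. As an opioid-death rate, 50 per 1000 would place about 88% of county opioid-involved deaths in 2000 clients (62% to 88% for county rates of 130 down to 92 per million), against the article's own account of who else is at risk. As an all-cause rate, it belongs to a different endpoint.

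The 30-per-1000 scenario, at about 53% of county opioid-involved deaths, is easier to reconcile with the rest of the article. On that footing, power for a 25% reduction is 57%, and RR 0.68 is needed for about 80%.

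The opioid-specific conclusion rests on the transferred national rate, the 95% opioid share and a cohort of 2000. It concerns the published cohort-based figure and makes no finding about the power of the county-wide comparison.

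**What to change.** In Power and sample size:

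1. State whether 50 and 30 per 1000 are all-cause or opioid-intoxication deaths, and give their source.
2. Stop presenting 81% at RR 0.75 as power for the primary outcome.
3. Make the 30-per-1000 scenario the base case (57% at RR 0.75; RR 0.68 for about 80%), unless registered county opioid deaths for 2013–2017 support a higher rate in the cohort.
4. Add power for the county-wide comparison, calculated from those registered counts.

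The cost is rewording and a short recalculation. The 2013–2017 counts are already part of the planned primary comparison, so no extra participants or data collection are needed. The stated cohort power for a 25% reduction becomes less favourable.

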### Opioid overdose

Defined as loss in consciousness and respiratory depression, opioid overdose is not a rare event among people who use opioids. Reports from Norway and Sweden have shown that the majority (> 70%) of heroin users have experienced at least one previous non-fatal overdose [16, 42, 43]. Estimations show that approximately one in 20 to one in 30 opioid overdoses leads to death [36]. Research describes an array of direct and indirect negative consequences of non-fatal opioid overdoses, such as pulmonary [44, 45] and cardiovascular complications [46], peripheral neuropathy [47], cognitive impairment [48] and rhabdomyolysis, which can lead to muscular problems, kidney injuries or failure [49]. Indirect injuries, such as injuries caused by falling, burns and assault, during loss of consciousness, are also rather frequently displayed [47].

As non-fatal overdoses are far more common than fatal opioid overdoses it is difficult to estimate the impact even of larger naloxone distribution programs. As non-fatal overdose commonly leads to both internal and external injuries it is important to focus both on reduction in mortality and reduction in morbidity. It is, however, impossible to predict whether a reversed opioid overdose would have been fatal, had naloxone not been administered, nor if potential injuries would have been avoided. This, the addition of societal factors that fluctuate over time, such as availability of drugs and potency of opioids, makes the estimated impact of OPEND on mortality and morbidity problematic. As research has shown that survival time exceeded 20–30 min in a majority of opioid related overdose fatalities, there is an opportunity for intervention [50]. By using naloxone, opioid overdoses can efficiently and safely be reversed by witnessing bystanders [51, 52].

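### The worked example behind the sample size implicitly counts each naloxone dose given as one death averted, so it does not support the claim that 2000 participants are enough

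*Protocol article*

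**What the plan says.** All places are in the protocol article.

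- **Power and sample size, power calculation.** The cohort is about 2000 people, half from OST and half from NEP. The comparison period gives "a total of 4 × 2000 = 8000 person years" and the intervention period "1.5 × 2000 = 3000 person years". At 50 deaths per 1000 person-years, a 25% reduction is required for 81% power. At 30 per 1000, a 32% reduction is required for 81% power, and a 25% reduction has 57%.
- **Power and sample size, feasibility argument.** From earlier studies the authors assume that "10–20% of those who received naloxone have used these doses" during follow-up. They say that the number of treated people who would otherwise have died cannot be established. They then take a fall from 30 to 20 deaths per 1000 person-years with 10% use, and reach 100 (10 × 10) "present overdose witnesses are required with access to naloxone for dose to be given in ten cases". The argument closes with "it is our belief that 2000 study participants", about 1000 from each setting, will suffice to detect significant mortality reductions.
- **Opioid overdose (Background).** Here the text states that "approximately one in 20 to one in 30 opioid overdoses leads to death".

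**The concern.** The first 10 in the example's 10 × 10 can only be the difference between 30 and 20 deaths. The second is the inverse of 10% use. No factor stands between a dose given and a death averted, so the conversion is implicitly one to one. That is the most favourable value it could take. It conflicts with the fatality range in the Background and with the caveat, in the same argument, that this fraction is unknown.

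The example is the protocol's only numerical argument that the reduction needed for adequate power could come from 2000 participants. A reader who trusts it could take a non-significant first result as evidence of no effect, when power at the effects implied by the protocol's own use and fatality figures may be well below 80%.

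**Working it through.** **1. Reproduce the stated power.** Two-proportion formula, two-sided 5%, person-years as denominators (8000 and 3000), pooled variance under the null and unpooled under the alternative:

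| Rate per 1000 | RR | Stated | Recomputed |
|---|---|---|---|
| 50 | 0.75 | 81% | 80.6% |
| 30 | 0.68 | 81% | 80.4% |
| 30 | 0.75 | 57% | 57.0% |

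The power arithmetic is sound. The question is only the step from doses to deaths.

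**2. Put the fatality factor into the worked example.**
- Ten doses avert 10/30 to 10/20 = 0.33–0.5 deaths, not ten. That is 1.1–1.7% of 30.
- Averting ten deaths takes 10 × 20 to 10 × 30 = 200–300 doses.
- At 10% use, that is 200/0.10 to 300/0.10 = 2000–3000 carriers per 1000 person-years, not 100.

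**3. Apply it to the whole cohort.** Assumptions: one use per user, the 10–20% falls within the 1.5-year window, 2000 recipients, and treated overdoses have the Background's average fatality.
- Uses: 2000 × 0.10 to 2000 × 0.20 = 200–400.
- Deaths averted: 200/30 to 400/20 = 6.7–20.
- Expected deaths in 3000 person-years: 90 at 30 per 1000, 150 at 50 per 1000.

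| Use, fatality | Averted | Reduction at 30/1000 (power) | Reduction at 50/1000 (power) |
|---|---|---|---|
| 10%, 1/30 | 6.7 | 7.4% (9%) | 4.4% (7%) |
| 10%, 1/20 | 10 | 11.1% (14%) | 6.7% (10%) |
| 20%, 1/30 | 13.3 | 14.8% (23%) | 8.9% (15%) |
| 20%, 1/20 | 20 | 22.2% (47%) | 13.3% (30%) |

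The implied RR runs from 1 − 0.222 = 0.78 to 1 − 0.044 = 0.96.

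**4. Compare with what is required for 81% power.**
- At 30 per 1000: 0.32 × 90 = 28.8 deaths averted. That takes 576–864 uses, or 1.4–4.3 uses per user (576/400 to 864/200).
- At 50 per 1000: 0.25 × 150 = 37.5 deaths averted. That takes 750–1125 uses, or 1.9–5.6 uses per user (750/400 to 1125/200).
- With one use each, 576–1125 uses means 29–56% of 2000 recipients, against the 10–20% assumed.

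**5. Vary the time window**, since the length of follow-up behind the 10–20% is not stated.
- Over three years: half the uses fall in 1.5 years, so 3.3–10 deaths are averted (3.7–11.1% at 30 per 1000).
- Per year, which the text does not say: 10–30 deaths are averted (11.1–33.3% at 30 per 1000; 6.7–20% at 50 per 1000). Only 20% use with 1/20 fatality at 30 per 1000 then reaches the required reduction.
- At the example's own 10% use, no window gives more than 15/90 = 16.7%.

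**The case against.** The strongest reply is that the protocol does not predict these effects. The 25% and 32% are reductions required for a given power, and the 57% shows what happens when one is missed. The protocol also says openly that deaths averted per dose cannot be established, describes ten cases of a dose being given rather than ten deaths averted, and words sufficiency as a belief. This stands in part: the one-to-one conversion is inferred from the arithmetic, not declared. But the caveat does not repair a calculation that then leaves the unknown factor out, nor does it support the firm conclusion drawn.

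A reader might go further and infer that the required reduction cannot be reached from the protocol's inputs. The document does not support that:
- The 10–20% is a share of recipients, not a count of uses. Kits hold two sprays and refills are planned, so repeat use is possible.
- People who decline the study get the same training and naloxone, and about 80% consent. As an illustration, 2000/0.8 = 2500 recipients would avert 8.3–25 deaths, or 9–28% of 90, with about 67% power at the top. That exceeds 25% but not 32%.
- Naloxone may be used mainly in severe overdoses, where fatality is above average.
- Training also covers calling an ambulance, airway management and recovery position.
- The protocol calls its calculation a minimum and mentions spread beyond OST and NEP, though without a figure.

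A reader might also infer that a realistic effect would most likely be missed. The power figures above concern only the 18-month window of the first analyses. The primary outcome runs over 2019–2023. If the same 2000 people are carried over five years before and 4.5 years after (10000 and 9000 person-years, an assumption), a sustained 22% reduction at 30 per 1000 has about 81% power. A 7% reduction still has only about 15%.

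**Conclusion.** The worked example is wrong as written. It omits the step from doses to deaths, and with the protocol's own fatality range its figure of 100 witnesses is too small by a factor of 20–30. Under the four assumptions in step 3 of the working, every combination falls short of the reduction required for 81% power in the 18-month window. Even the most favourable one, 22.2% at 30 per 1000, lies below the 25% to which the protocol gives 57% power. Relaxing those assumptions can raise the effect, and the longer primary window can raise the power. The conclusion is therefore that the example leaves the required reduction unsupported, not that the reduction is impossible or that the study will fail. The power calculation itself reproduces and is not in question.

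**What to change.** In Power and sample size:
1. Add the 1/20–1/30 fatality factor to the example, so that averting ten deaths corresponds to about 200–300 doses and 2000–3000 carriers at 10% use.
2. Give the implied RR range (about 0.78–0.96) and its power for the 18-month window: about 9–47% at 30 per 1000 and 7–30% at 50 per 1000. State the assumptions: one use per user, use within 1.5 years, recipients equal to participants, average fatality in treated overdoses.
3. Replace the unconditional sufficiency statement with what would be needed for the required reductions. At the protocol's fatality range and one use each, that is use by 29–43% of 2000 recipients (30 per 1000) or 38–56% (50 per 1000). At 10–20% use, it is 1.4–4.3 or 1.9–5.6 uses per user. With one use each at 10–20% use, the fatality share needed is 28.8/400 to 28.8/200 = 7–14%, or 37.5/400 to 37.5/200 = 9–19%.

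The cost is text only. Stated power at effects implied by the protocol's figures becomes less favourable. Enrolment, design and analysis do not change.
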